## Abstract

**Background:**

Bladder cancer diagnosis relies on cystoscopy and transurethral resection of bladder tumor (TURBT) for histopathological evaluation, but this process is time consuming, costly, and subject to variability. Optical coherence tomography (OCT) offers real-time, high-resolution imaging as a potential alternative.

**Objective:**

This study primarily aims to assess the feasibility of capturing in vivo cross-sectional images of the bladder wall using a novel microelectromechanical systems (MEMS)-based OCT catheter. Secondary objectives include evaluating measurement duration, assessing tumor stage and grade from OCT images in comparison with histopathology, determining the catheter’s ability to image resection beds, and comparing OCT-based tumor staging with white light cystoscopy assessments.

**Methods:**

This single-center feasibility study at Amsterdam University Medical Center includes patients undergoing TURBT for suspected bladder tumors. Eligible patients must be aged 18 years or older, have at least 1 cystoscopically accessible tumor, and must be physically fit for TURBT. Exclusion criteria include pregnancy, tumors larger than 2 cm, more than 5 tumors, isolated flat lesions, or tumors solely at the bladder neck. The primary end point assesses the procedural feasibility of OCT imaging, while the secondary end points evaluate tumor staging, grading, and correlation with histopathology. Up to 25 patients will be enrolled, with feasibility achieved if diagnostic images are obtained in more than 60% of the cases. OCT imaging is performed before and after tumor resection, with histopathological results used for comparison. Patients will be monitored for adverse events for 4 weeks after the procedure, after which study participation ends.

**Results:**

As of November 2025, 16 participants have been enrolled, and 13 have successfully completed the study procedure. The projected end date of the study is November 2025, and results are expected to be published in March 2026.

**Conclusions:**

This study is expected to provide key insights into the feasibility and clinical utility of the newly developed MEMS-based forward-looking OCT system for real-time bladder imaging during TURBT. This study will lay the groundwork for a larger trial to evaluate its diagnostic accuracy in staging and grading bladder cancer.

**Trial Registration:**

ClinicalTrials.gov NCT06679920; https://clinicaltrials.gov/study/NCT06679920

**International Registered Report Identifier (IRRID):**

DERR1-10.2196/76644

## Introduction

The current diagnostic process for bladder cancer involves a cystoscopy followed by transurethral resection of the bladder tumor (TURBT) [1]. A TURBT is undertaken to obtain material for histopathology, which is required to confirm the malignant nature of the lesion and, if so, to determine the invasion and grade of the tumor [1]. In some patients, a repeat TURBT is necessary to ensure complete resection and confirm the histopathological stage [1]. Determining the histopathological stage and grade is essential for an appropriate treatment plan. If the tumor is muscle invasive, the available treatment options are radical cystectomy or trimodality therapy [2]. Treatment of non–muscle-invasive bladder cancer comprises TURBT, followed by regular cystoscopy, and, depending on the differentiation grade of the tumor, additional Bacille Calmette-Guérin or chemotherapy instillations [1].

Although the histopathological result is currently regarded as the gold standard, there remains significant interobserver variability, which may have a considerable impact on treatment decisions [3]. Furthermore, the current diagnostic process places a substantial burden on patients with bladder cancer and results in substantial health care costs [4,5]. Both surgical planning and the histopathological process are time consuming as well. Therefore, there is a need for an alternative option to determine the tumor grade and stage in real time.

The primary objective of this study is to investigate the feasibility of capturing in vivo cross-sectional images of the bladder wall in patients with bladder cancer using the newly developed MEMS-based OCT catheter. Secondary objectives are to evaluate the duration of the OCT measurements, determine the tumor stage based on OCT images and test for an association with histopathological results, determine the grade of the tumor based on OCT images and test for an association with the histopathological results, determine if the OCT catheter is able to acquire evaluable images of the bladder wall after resection of the tumor, and compare the tumor grade and stage estimated during WLC with the tumor grade and stage based on the OCT images.

This is a single-group; idea, development, exploration, assessment, and long-term (IDEAL) phase 2a (development) [25]; single-center feasibility study.

## Methods

### Study Population and Setting

The study population comprises adult patients with a suspected bladder tumor, either non–muscle-invasive bladder cancer or muscle-invasive bladder cancer, planned for a TURBT. This study is performed at the Amsterdam University Medical Center (UMC). The trial has been registered on ClinicalTrials.gov (NCT06679920).

### Eligibility Criteria

The eligibility criteria are presented in Textbox 1.

Inclusion and exclusion criteria.
**Inclusion criteria**
Aged older than 18 yearsHave at least 1 suspected bladder tumor seen on cystoscopyHave a bladder that is accessible for cystoscopyBe in a physical condition to undergo transurethral resection of the bladder tumorMust be fully informed about the study and should provide written informed consent before any study-related investigation or intervention
**Exclusion criteria**
Pregnant or lactating womenOnly tumor site at the bladder neckTumor larger than 2 cm in diameterMore than 5 tumors presentOnly flat suspected lesions

### Study Procedures

#### Standard Procedure

The standard procedure is the TURBT. After regional or general anesthesia, a resectoscope is inserted into the bladder through the urethra. First, endoscopic inspection of the bladder wall is performed to identify tumors and suspicious lesions. Then, the identified tumors are resected using a loop wire with electric current. After resection of the tumor and retrieval of the resected tissue, the resection bed and edges are cauterized to ensure hemostasis. Subsequently, the resectoscope is removed, and, in most cases, a catheter will be inserted. Resected tissue is sent to pathology to determine the definitive stage and grade. Figure 1 provides an overview of the standard procedure and the schedule of the interventions.

**Figure 1 figure1:**
[figure not shown]
Schematic overview of the standard procedure and timing of the study interventions during transurethral resection of the bladder tumor.

#### OCT Measurements

During the standard TURBT procedure, the OCT measurements will be performed. After the inspection of the bladder and before the resection of the identified bladder tumors, the OCT catheter will be inserted through the working channel of the rigid resectoscope. The tumors will then be imaged with the OCT catheter tip at approximately 1 cm from the tumor. Approximately 5 measurements will be performed for each suspected lesion and tumor and 3 for a selected region of normal bladder wall. When the OCT measurements are finished, the OCT catheter is removed from the bladder, and the urologist will continue with the standard procedure. The resection of the tumors is performed according to standard care. However, the pathology specimens of each separate tumor will be collected and numbered according to the tumor numbers used during the OCT measurements and sent to the pathologist. After completion of the resection, the OCT catheter will be reinserted through the working channel of the rigid resectoscope, and approximately 3 OCT measurements will be performed on each resection bed. After these measurements, the OCT catheter will be removed from the bladder, and the urologist will continue with the standard procedure (Figure 1).

### Study Outcomes

#### Primary End Point

The primary end point comprises two components:

Procedural feasibility of OCT imaging will be determined by the ability to generate images of the normal bladder wall and bladder tumors, as assessed by the operating urologist. Procedural feasibility will be achieved if diagnostic images of the tumor and normal bladder are obtained in more than 60% of the patients.Feasibility based on image use will be evaluated as the percentage of images suitable for diagnosis out of the total number of OCT images obtained. A percentage greater than 80% is regarded as feasible.

#### Secondary End Point

The secondary outcomes include (1) duration of the OCT measurements, (2) concordance between the OCT-based diagnosis of tumor invasion and histopathological diagnosis, (3) concordance between the OCT-based diagnosis of tumor grade and the histopathological diagnosis, (4) the ability of the OCT catheter to acquire evaluable images of the resection bed, and (5) concordance between intraoperative WLC assessments and OCT findings on tumor grade and invasion.

### Study Timeline

Patients will be identified at the outpatient clinic, and patients meeting the inclusion and exclusion criteria who provide informed consent will be scheduled for TURBT within 6 weeks of identification. The TURBT and the OCT catheter procedure will be performed as described previously. The procedural timeline of the TURBT is illustrated in Figure 1. After undergoing TURBT, participants will continue with standard treatment. Serious adverse events (AEs) will be monitored and recorded for a period of 4 weeks. Study participation will conclude at the end of this monitoring period.

### Sample Size and Enrollment

To date, no human study assessing the feasibility of this new MEMS-based OCT catheter for bladder cancer has been conducted. Therefore, a sample size calculation is not possible. The goal of this study is to test the technical and procedural feasibility of the device in a single-center, single-intervention, small prospective cohort study. In this IDEAL stage 2a study, up to 25 patients who undergo technically successful OCT measurements will be enrolled. Because the feasibility cutoff is set at 60%, inclusion will stop when a feasible procedure is performed in 15 patients. The findings of this study will inform sample size calculations for future investigations.

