### Data Collection and Management

Data collection and analysis will be conducted in accordance with Good Clinical Practice guidelines to ensure data integrity and reliability. Outcome, baseline, and other trial-related data will be systematically collected from both paper-based and electronic sources, including case report forms completed during TURBT and electronic patient records. All data will be securely stored in Castor Electronic Data Capture, a validated electronic data capture system designed to prevent unauthorized access and ensure compliance with the General Data Protection Regulation. To maintain data completeness and allow for comprehensive analysis, all information collected up to the point of participant withdrawal or protocol deviation, including OCT measurements, cystoscopic video recordings, and histopathological findings, will be retained for subsequent evaluation.

To safeguard participant confidentiality, each enrolled individual will be assigned a unique participant ID code, with a corresponding participant ID code list maintained only when necessary for data traceability. The principal investigator will be responsible for securing the key to this code. In addition, individual OCT measurements will be assigned specific identifiers to ensure structured and organized data management. OCT data and cystoscopic video recordings will initially be stored on the OCT system and subsequently transferred to the local drive of the urology department on the secure Amsterdam UMC computer server using an encrypted external hard drive immediately after acquisition. Access to the local drive will be restricted to study investigators and the study monitor to ensure data security and confidentiality. Once the transfer is successfully completed, the data will be permanently deleted from the external hard drive. Upon completion of the study, all OCT images and cystoscopic video recordings will also be removed from the OCT system.

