Robust data management protocols will be implemented to ensure data accuracy, security, and traceability. Data entry, coding, and security procedures will be conducted within Castor Electronic Data Capture, incorporating an audit trail to track all modifications. Paper-based case report forms will be securely stored, signed, and archived, while electronic data will be subject to automated validation procedures. Univariate data validations will be embedded within the Castor system, whereas multivariate validations, derivations, and calculations will be incorporated where applicable and documented in a dedicated data validation and derivation plan. The comprehensive data management strategy is outlined in this study’s data management plan. In accordance with regulatory requirements, all participant data will be securely retained for a period of 15 years.

Missing data will be descriptively reported and discussed. Missing OCT measurements will be reported as part of the main outcomes. Missing histopathological data are not expected; in case of missing data, it will be described in the secondary outcomes section.

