### Statistical Methods

#### Primary Outcomes

Procedural feasibility will be achieved if images of both the tumor and normal bladder are obtained in more than 60% of the patients. The feasibility based on OCT imaging will be assessed by determining the percentage of images suitable for diagnosis out of the total number of images obtained in all patients. A panel, consisting of 2 urologists and 1 PhD candidate, blinded to clinical information, will individually analyze the OCT images. They will determine if the OCT images are suitable for diagnosis. The OCT measurements will be scored as suitable if (1) tissue is observed on the OCT image, (2) the tissue is within the focus range of the OCT, and (3) no movement artifacts are observed in the image. In case of disagreement, an experienced research fellow will be added to the panel, and the scoring will be discussed within this panel. Consensus will be reached when 3 of the 4 panel members agree. The data will be described and presented as percentages with 95% CIs. No statistical tests will be performed.

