## Results

As of November 2025, 16 participants have been enrolled, and 13 have already successfully completed the study procedure. The projected end date of this study is November 2025, and results are expected to be published in March 2026.

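### The cap of 25 is counted in patients with technically successful OCT, and the protocol does not say whether technical failures are in the denominator of the 60% criterion

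*Protocol article*

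**What the plan says.** Four parts of the protocol article bear on who is counted.

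- **Sample Size and Enrollment** gives the aim as testing technical and procedural feasibility. It then states that "up to 25 patients who undergo technically successful OCT measurements will be enrolled", and adds: "Because the feasibility cutoff is set at 60%, inclusion will stop when a feasible procedure is performed in 15 patients". It defines neither a technically successful measurement nor how that differs from a feasible procedure.
- **Abstract, Methods** has no success condition on the cap: "Up to 25 patients will be enrolled, with feasibility achieved if diagnostic images are obtained in more than 60% of the cases".
- **Primary End Point** and **Statistical Methods, Primary Outcomes** set the criterion: "Procedural feasibility will be achieved if diagnostic images of the tumor and normal bladder are obtained in more than 60% of the patients", and "Procedural feasibility will be achieved if images of both the tumor and normal bladder are obtained in more than 60% of the patients". Neither says whether the patients are those enrolled, those in whom OCT was attempted, or those with technical success.
- **Results** reports progress: "16 participants have been enrolled, and 13 have already successfully completed the study procedure".

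Data Collection and Management adds that "Missing OCT measurements will be reported as part of the main outcomes" and that "all information collected up to the point of participant withdrawal or protocol deviation" is kept. Neither sentence assigns a failed patient to a denominator.

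**The concern.** The first primary end point component asks in what share of patients imaging works. If the counted cohort is defined by technical success, some of the failures that the study should measure may lie outside it. Two things could follow from the literal wording: a patient with a technical failure uses no place in the cap, and the same patient may be missing from the denominator of the 60% criterion.

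No statistical test is planned for the primary outcome, so the percentage and its 95% CI are the whole primary result. The findings are also meant to inform sample sizes for later studies, so an inflated rate would carry forward.

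**Working it through.** **1. The plan's own figure.** The cap is 25 and the cutoff is 60% (Sample Size and Enrollment). 0.60 × 25 = 15, which reproduces the number of feasible procedures at which inclusion stops. The product does not show what the 25 are: it holds for 25 attempted patients and equally for 25 technically successful patients of whom 15 are feasible.

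**2. The sections side by side.** Under Informed Consent, consent comes before enrolment. Under Study Timeline, TURBT is scheduled after consent. Technical success therefore cannot be known when a patient is enrolled. The Results section uses *enrolled* in this wider sense (16 against 13), as does the Abstract. Only Sample Size and Enrollment attaches success to the count.

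**3. Direction of the bias if failures are left out.** Let *t* be the probability that an attempt is technically successful, and *f* the probability of a feasible procedure given technical success. Assume that a feasible procedure is always technically successful.

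- Rate over all attempts = *t × f*
- Rate over technically successful patients = *f*
- Ratio of the second to the first = 1/*t*, which exceeds 1 whenever any attempt fails technically

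The documents give neither *t* nor *f*, so these values are assumptions:

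| *t* | *f* | Over all attempts | Over technical successes |
|---|---|---|---|
| 0.8 | 0.70 | 0.8 × 0.70 = 56% | 70% |
| 0.8 | 0.60 | 0.8 × 0.60 = 48% | 60% |
| 0.5 | 1.00 | 0.5 × 1.00 = 50% | 100% |

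In the first and third rows, the two denominators fall on opposite sides of 60%.

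**4. The cap.** If only technical successes use places, filling 25 places takes 25/*t* attempts on average: 25/0.8 = 31.2, or 25/0.6 = 41.7 (assumed *t*).

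**5. Fifteen feasible procedures over different denominators.** Exact (Clopper-Pearson) 95% limits for *x* of *n* are the 0.025 quantile of Beta(*x*, *n* − *x* + 1) and the 0.975 quantile of Beta(*x* + 1, *n* − *x*), with an upper limit of 1 when *x* = *n*.

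| Count | Rate | Exact 95% CI |
|---|---|---|
| 15/15 | 100% | 78.2–100% |
| 15/25 | 60% | 38.7–78.9% |
| 15/30 | 50% | 31.3–68.7% |

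The first row needs failures to be dropped and every technically successful procedure to be feasible.

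**6. Reported progress, as an illustration.** 16 − 13 = 3 enrolled patients are not among the completers. If all 3 were failures, which the text does not say:

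- failures counted: 13/16 = 81%, CI 54–96%
- failures left out: 13/13 = 100%, CI 75–100%

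Both estimates exceed 60%. The lower confidence limit is below 60% in the first case and above it in the second.

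**The case against.** The strongest reply is that the authors probably mean all enrolled patients. The Abstract has no success condition, the Results section counts patients who have not completed as enrolled, and missing OCT measurements are to be reported with the main outcomes. Technical success may also be a separate condition, such as a working catheter and system. Counting by it would then not select on the primary end point itself. This is also a small IDEAL phase 2a study with descriptive results. All of this stands, and it limits the point to an ambiguity that needs to be closed.

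A reader might infer more than the text supports in three ways:

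- **That failures will be replaced without limit and excluded.** No section states a replacement rule or an exclusion from analysis.
- **That the stop at 15 proves that 25 counts attempts.** Step 1 shows that it fits either reading.
- **That the 3 non-completers failed.** The text says that 13 have *already* completed, so the others may simply have been waiting for the procedure.

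The reply does not supply a denominator. Reporting missing measurements and retaining data are not the same as counting a patient as a non-success. If technical success is a separate condition, the patients lost would still be technical failures in a study of technical feasibility.

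**Conclusion.** The point holds as a contradiction over the cap and an undefined denominator for a primary criterion. If technical failures were left out, the rate would be biased upward by the factor 1/*t*, assuming that every feasible procedure is also technically successful. The size is unknown because the documents give no technical success rate. The assumed values show that the conclusion against 60% could change, while the reported progress figures leave the point estimate above 60% under either denominator. The documents do not establish that failures will be dropped or that the design is biased as run.

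**What to change.** Reconcile the Abstract, Primary End Point, Sample Size and Enrollment, and Primary Outcomes sections.

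- Define the cap of 25 and the denominator of the 60% criterion as all patients in whom OCT imaging is attempted. Attempted means that insertion of the OCT catheter was started or intended at TURBT, and it includes device or system failure before insertion.
- Count technical failures and no-image cases as non-successes.
- Define technical success, and report the enrolled, attempted, technically successful and feasible counts, with reasons for the differences.

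The projected study end is November 2025, so enrolment may be over. In that case apply the denominator and reporting parts, and fix them before the primary result is calculated.

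**Cost.** The reported rate may be lower. If enrolment is still open, an attempt-based cap also changes recruitment, because 25 attempts may be reached before 15 feasible procedures. From the exact binomial distribution, the chance of that is 1 − P(at least 15 of 25): 0.79, 0.41, 0.10 and 0.006 at assumed true feasibility rates of 0.5, 0.6, 0.7 and 0.8.

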### Data Collection and Management

Data collection and analysis will be conducted in accordance with Good Clinical Practice guidelines to ensure data integrity and reliability. Outcome, baseline, and other trial-related data will be systematically collected from both paper-based and electronic sources, including case report forms completed during TURBT and electronic patient records. All data will be securely stored in Castor Electronic Data Capture, a validated electronic data capture system designed to prevent unauthorized access and ensure compliance with the General Data Protection Regulation. To maintain data completeness and allow for comprehensive analysis, all information collected up to the point of participant withdrawal or protocol deviation, including OCT measurements, cystoscopic video recordings, and histopathological findings, will be retained for subsequent evaluation.

To safeguard participant confidentiality, each enrolled individual will be assigned a unique participant ID code, with a corresponding participant ID code list maintained only when necessary for data traceability. The principal investigator will be responsible for securing the key to this code. In addition, individual OCT measurements will be assigned specific identifiers to ensure structured and organized data management. OCT data and cystoscopic video recordings will initially be stored on the OCT system and subsequently transferred to the local drive of the urology department on the secure Amsterdam UMC computer server using an encrypted external hard drive immediately after acquisition. Access to the local drive will be restricted to study investigators and the study monitor to ensure data security and confidentiality. Once the transfer is successfully completed, the data will be permanently deleted from the external hard drive. Upon completion of the study, all OCT images and cystoscopic video recordings will also be removed from the OCT system.

Robust data management protocols will be implemented to ensure data accuracy, security, and traceability. Data entry, coding, and security procedures will be conducted within Castor Electronic Data Capture, incorporating an audit trail to track all modifications. Paper-based case report forms will be securely stored, signed, and archived, while electronic data will be subject to automated validation procedures. Univariate data validations will be embedded within the Castor system, whereas multivariate validations, derivations, and calculations will be incorporated where applicable and documented in a dedicated data validation and derivation plan. The comprehensive data management strategy is outlined in this study’s data management plan. In accordance with regulatory requirements, all participant data will be securely retained for a period of 15 years.

Missing data will be descriptively reported and discussed. Missing OCT measurements will be reported as part of the main outcomes. Missing histopathological data are not expected; in case of missing data, it will be described in the secondary outcomes section.

